## Abstract

**Background:**

Peritoneal dialysis is an important type of renal replacement therapy for uremic patients. In peritoneal dialysis, fluids fill in and flow out of the abdominal cavity three to five times per day. Usually, the fluid is packed in a polyvinyl chloride (PVC) bag. Safety concerns have arisen over di-(2-ethylhexyl) phthalate, which is essential in the formation of PVC materials. In 2011, the National Development and Reform Commission of China released a catalog of industrial structural adjustments, mandating the elimination of PVC bags for intravenous infusion and food containers. Although bags for peritoneal dialysis fluid were not included in the elimination list, several manufacturers began to develop new materials for fluid bags. HUAREN peritoneal dialysis fluid consists of the same electrolytes and buffer agent as in Baxter fluid, but is packed in bags that do not contain PVC. This multicenter randomized controlled trial was designed to compare peritoneal dialysis fluid packed in non-PVC-containing and PVC-containing bags. Further, the study sought to determine the proper dose of peritoneal dialysis fluid and the actual survival rates of Chinese patients undergoing peritoneal dialysis.

**Methods/Design:**

The study participants are adults undergoing continuous ambulatory peritoneal dialysis for 30 days to 6 months. All eligible patients are randomized (1:1) to peritoneal dialysis with Baxter and HUAREN dialysis fluids (initial dose, 6 l/day), with dosages adjusted according to a unified protocol. The primary outcomes are the 1-, 2-, 3-, 4-, and 5-year overall survival rates. Secondary outcome measures include technique survival rates, reductions in estimated glomerular filtration rate, nutritional status, quality of life, cardiovascular events, medical costs and drop-out rates. Safety outcome measures include adverse events, changes in vital signs and laboratory parameters, peritonitis, allergies, and quality of products.

**Discussion:**

This study is the first to evaluate the long-term safety and effectiveness of a non-PVC packed peritoneal dialysis fluid. The effects of plasticizer on patient long-term survival will be determined. The characteristics of Chinese patients undergoing peritoneal dialysis will be determined, including proper dose, technique survival rates, patient survival rates, and medical costs.

**Trial registration:**

Clinicaltrials.gov NCT01779557.

**Electronic supplementary material:**

The online version of this article (doi:10.1186/s13063-015-1131-1) contains supplementary material, which is available to authorized users.

## Background

Peritoneal dialysis is a major type of renal replacement therapy. Worldwide, up to about 200,000 patients, or about 12 % of all patients with end-stage renal disease, currently undergo peritoneal dialysis. This therapy involves filling of the abdominal cavity and drainage of peritoneal dialysis fluids three to five times per day, with each patient requiring 6 to 10 liters of peritoneal dialysis fluid per day. *Dianeal*® (Baxter Inc.) is the most widely used commercially available peritoneal dialysis fluid in China and has been used for many years. The dialysis fluid is packed in a bag made of polyvinyl chloride (PVC). The plasticizer most frequently added to PVC to improve its flexibility is di-(2-ethylhexyl) phthalate (DEHP). However, DEHP can be released by PVC materials because it is not chemically bonded to the polymer. Moreover, DEHP can be incorporated into the human body and be detected in body fluids and tissues. It has been shown that DEHP is toxic to the liver, testis, and other organs [1, 2], and that its major metabolite, mono-(2-ethylhexyl) phthalate, is even more toxic than DEHP. Use of this plasticizer has aroused great concern regarding the safety of PVC materials [3, 4]. Many daily utensils contain plasticizer, which might be harmful to human health [5–10]. Medical tubing and bags made of PVC, such as bloodlines for hemodialysis and bags for peritoneal dialysis fluids, might expose patients to considerable amounts of plasticizer and its hydrolytic metabolites. The safety of plasticizers in medical materials has been evaluated by the USA, Japan, and the European Union for more than 10 years. In 2011, the Chinese National Development and Reform Commission released a catalog of industrial structural adjustments [11], mandating the elimination of PVC bags for infusion and food containers. Although bags for peritoneal dialysis fluids were not included on that list, the presence of higher concentrations of DEHP in patients receiving continuous ambulatory peritoneal dialysis [12] has led manufacturers to seek new materials for peritoneal dialysis bags. HUAREN peritoneal dialysis fluid is a non-PVC packed Chinese product that contains the same electrolytes and buffering agent as Baxter fluid. Several studies have investigated non-PVC peritoneal dialysis fluid products (e.g., *bicaVera*®, *balance*®) [13, 14]. However, because the packaging material is the only difference between HUAREN and Baxter peritoneal dialysis fluids, a study comparing the two should clearly show the effects of plasticizer.

The targeted small solute clearance for Asian patients is *Kt*/*V* ≥ 1.7 [15], although other targets have been suggested [16–19]. The proper dose required to attain this goal may differ among populations, owing to differences in race, ethnicity, and food consumption. A dosage of 8 l/day is often used in Western populations, whereas the dosage for Asians is usually 6 l/day. Our previous research showed that an initial dose of 6 l/day could provide adequate peritoneal dialysis for 48 weeks [20], but the proper dosage afterwards remains unclear. The proper dosage for Chinese patients receiving continuous ambulatory peritoneal dialysis is unclear, as are their mid- to long-term survival rates. This study includes a protocol for adjusting dosage based on each patient’s medical status. With a 5-year follow-up period, the ‘proper’ dosage and ‘real’ situations of Chinese patients receiving continuous ambulatory peritoneal dialysis can be determined.

## Methods/Design

### Study design

This is a prospective, multicenter, randomized controlled trial with non-inferiority design. Patients will be randomized to HUAREN or Baxter peritoneal dialysis fluid (Fig. 1).

**Fig. 1 Fig1:**
[figure not shown]
Study design. This is a randomized controlled trial. The eligible patients will be randomly allocated to two groups, Baxter group or HUAREN group. Patients will use Baxter or HUAREN peritoneal dialysis fluid for 5 years. The outcomes will be analyzed and compared. ESRD, end-stage renal disease; PD, peritoneal dialysis

### Patients

Male and female patients aged ≥18 years diagnosed with end-stage renal disease who undergo continuous ambulatory peritoneal dialysis for 30 to 180 days are included. Patients diagnosed with diabetic kidney disease have a residual glomerular filtration rate of 3 to 15 ml/min [21], whereas patients with other renal diseases have a residual glomerular filtration rate of 3 to 10 ml/min.

All patients must provide written informed consent before undergoing any study-related procedures.

Patients are excluded if: they have acute renal failure; are candidates for kidney transplantation; are undergoing hemodialysis; have an exit site infection, tunnel infection or peritonitis according to Peritoneal Dialysis Standard Operating Procedure [22]; are anti-HIV positive; are allergic to any component of dialysis fluids; have a systemic infection, malignancy, liver cirrhosis, severe congestive heart failure, anemia (hemoglobin <80 g/l), malnutrition (albumin <28 g/l), refractory hypertension, high peritoneal transportation (*D*/*P*_Cr_ > 0.81); or are pregnant or lactating. Patients with poor compliance or a history of alcoholism or drug abuse are also excluded.

Patients are being recruited from 50 peritoneal dialysis centers throughout China. The study protocol was approved by the ethics committee of each center (Additional file 1) and is conducted according to the Declaration of Helsinki [23] and the Good Clinical Practices guidelines of the China Food and Drug Administration [24]. The study has been registered at www.clinicaltrials.gov, number NCT01779557.

### Randomization

Patients are centrally randomized 1:1 to HUAREN or Baxter peritoneal dialysis fluid, using a randomization chart generated by a biometrician blinded to clinical treatment. Physicians and nurses are also blinded to the randomization process, and each patient can be randomized only once. All procedures are under the supervision of an independent clinical research organization.

### Interventions

#### HUAREN group

Patients randomized to the HUAREN group will receive HUAREN dialysis fluid, a medical product that has been available in China for years. All the ingredients of HUAREN peritoneal dialysis fluid are identical to those of Baxter peritoneal dialysis fluid except for the packaging material, in that HUAREN peritoneal dialysis fluids are packed in bags made of non-PVC materials.

#### Baxter group

Patients randomized to the Baxter group will receive Baxter *Dianeal* dialysis fluid. This product contains 1.5 % dextrose as an osmotic agent and 40 mmol/l lactate as a buffering agent. The pH of this dialysis fluid is 5.5, and total osmotic pressure is 346 mOsm/kg. Other ingredients include 1.75 mmol/l Ca^2+^, 0.25 mmol/l Mg^2+^, 132 mmol/l Na^+^, and 96 mmol/l Cl^−^. Baxter dialysis fluids are packed in bags made of PVC materials.

During the screening period, all patients receive HUAREN dialysis fluid. After randomization, patients receive the allocated dialysis fluid.

#### Protocol for dosage adjustment

The initial dose in the two groups is 6 l/day, allowing three fluid exchanges. If *Kt*/*V*_total_ < 1.7, the dose is increased to 8 l/day, allowing four fluid exchanges. If *Kt*/*V*_total_ is ≥ 1.7, but with volume overload (e.g., heart failure, serous cavity effusion, moderate or severe edema), salt and water intake is restricted and diuresis starts. If this is insufficient, dextrose concentration is increased to 2.5 % or 4.25 %, depending on clinical demands. If a patient’s condition does not improve after administration of >6 l of fluid containing 2.5 % dextrose or >2 l of fluid containing 4.25 % dextrose, the dosage is increased to 8 l/day.

If *Kt*/*V*_total_ ≥ 1.7 and the patient is euvolemic, but with uremic manifestations, such as nausea, vomiting, or pruritus, the dose is increased from 6 l/day to 8 l/day.

Dosage changes from 8 l/day to 10 l/day should follow the same principle and procedure (Fig. 2).

**Fig. 2 Fig2:**
[figure not shown]
Dosage adjustment protocol. The initial dosage is 6 l/day; then the solute clearance, water removal, and clinical manifestation are evaluated. If *Kt*/*V* < 1.7, dosage should be increased. If there is a volume overload, salt and water intake, diuretics, and dextrose concentration should be modified before changing dosage. When the dosage is ≥ 12 l/day and *Kt*/*V* < 1.7, the treatment adaptation fails. Physicians should be flexible in choosing optimal therapies to protect patients from life-threatening circumstances. The *Kt*/*V* and creatinine clearance rate should be re-evaluated 2 weeks after each patient’s situation stabilizes

### Outcomes

The primary outcome measure is patient survival rates at 1, 2, 3, 4, and 5 years. The secondary outcome measures include peritoneal dialysis technique survival rates of 1, 2, 3, 4, and 5 years; estimated decline in glomerular filtration rate, nutritional status (represented as serum albumin and Subjective Global Assessment Score [25]), quality of life (described by the 36-Item Short-Form Health Survey [26]), cardiovascular events (cardiac sudden death, myocardial infarction, severe arrhythmia, carotid plaque, heart failure, cardiovascular intervention, coronary heart disease without myocardial infarction, stroke or transient ischemic attack, peripheral artery disease), increments of dialysis dosage from baseline to the end, and drop-out rates. Medical costs are also recorded.

Safety evaluations include adverse events and severe adverse events, marked changes of vital signs and laboratory test results, peritonitis (infectious or chemical), allergy to ingredients of peritoneal dialysis fluids and materials of bags and tubing, and quality of dialysis product. Evaluation of product quality includes the transparency of fluid bags, the tightness of connections, and the legibility of labels and texts on packaging.

### Sample size

The sample size is based on both Chinese facilities containing large numbers of patients [27–31] and the Chinese National Renal Data System [32], consisting of smaller units. We have estimated that the mean 5-year survival rate of patients using Baxter dialysis fluid is about 50 %, with a hazard ratio of 1.31. If the recruitment lasts 2 years and the observation 5 years, with *β* = 0.8, a one-sided *α* for the *t* test = 0.025, and 15 % censored data in each group, 310 patients per group will be needed. With a 20 % drop-out rate, 750 patients should be enrolled in this study.

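### The 15 % censoring input is either impossible or undefined, and on neither reading do the stated inputs give 310 patients per group

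*Protocol article*

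**What the plan says.** All of the inputs stand in the Sample size section of the protocol article.

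- Survival: the "mean 5-year survival rate of patients using Baxter dialysis fluid is about 50" %, "with a hazard ratio of 1.31".
- Timing: "If the recruitment lasts 2 years and the observation 5 years".
- Error rates: one-sided α of 0.025 and a β of 0.8, which can only sensibly mean 80 % power.
- Censoring: "15 % censored data in each group", with no definition.
- Result: 310 patients per group, followed by "With a 20 % drop-out rate, 750 patients should be enrolled in this study".

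The Study design section describes a "prospective, multicenter, randomized controlled trial with non-inferiority design", and allocation is 1:1. The Statistics section analyses survival by a Cox model, with non-inferiority judged from the 95 % confidence interval of the hazard ratio. It makes the per-protocol set primary and requires outcome data and good compliance for membership.

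**The concern.** In a Cox analysis a patient is censored either by being alive at the end of observation or by leaving sight earlier. The survival assumption already fixes the first kind at about half of the Baxter arm. A censored share of 15 % cannot sit beside it unless the figure covers only the second kind, and the paragraph does not say that it does. A second figure for leaving early, 20 %, follows in the next sentence, again undefined.

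The precision of the hazard ratio is governed by the number of deaths, and the censoring input is what turns patients into deaths. If that input is wrong or mislabelled, the stated size and power may not follow from the stated assumptions. For a non-inferiority trial, too few deaths means a wide interval and a real chance of an inconclusive result.

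**Working it through.** **Inputs from the Sample size section.** Baxter 5-year survival 0.50; hazard ratio 1.31; one-sided α 0.025 (z = 1.960); power 0.80 (z = 0.842); recruitment 2 years; observation 5 years; 15 % censored; 20 % drop-out; 310 per group (620); 750 enrolled.

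**Assumptions of this check.** 1.31 is the non-inferiority bound (the article does not call it one); the true hazards are equal when power is computed; survival and loss are exponential. Follow-up is either a fixed 5 years or 5 to 7 years with uniform entry.

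**1. Deaths needed.** Schoenfeld: D = 4(z_α + z_β)² / (ln 1.31)² = 4 × 7.849 / 0.0729 = 430.6, so 431. Freedman's formula gives 436.

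**2. Share alive at the end, Baxter arm.** λ = ln 2 / 5 = 0.1386 per year.

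- Fixed 5 years: 50 %.
- 5 to 7 years: (e^(−5λ) − e^(−7λ)) / 2λ = (0.500 − 0.379) / 0.277 = 43.7 %.
- Survival would fall to 15 % only at ln(1/0.15) / 0.1386 = 13.7 years.

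**3. Trying to reproduce 310: 15 % as total censoring.** 431 / 0.85 / 2 = 253.5, so 254 per group.

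**4. Trying to reproduce 310: 15 % as early loss.** With a loss hazard η = −ln 0.85 / 5 = 0.0325, the chance of an observed death within 5 years is λ/(λ+η) × (1 − e^(−5(λ+η))) = 0.810 × 0.575 = 0.466 on Baxter. It is 0.557 at hazard ratio 1.31. Averaging over 5 to 7 years gives 0.519 and 0.612. A cruder method multiplies the no-loss death probability by 0.85. Patients per group = 431 / (2 × death probability):

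| Follow-up | Method | Baxter probability | Mean of both arms |
|---|---|---|---|
| 5 years | exponential loss | 463 | 421 |
| 5 years | × 0.85 | 508 | 462 |
| 5 to 7 years | exponential loss | 416 | 381 |
| 5 to 7 years | × 0.85 | 451 | 414 |

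The range is about 381 to 508. At one-sided 0.05, which is not the stated level, no loss, fixed 5 years and the mean death probability give 309.3. That resembles 310 but leaves the 15 % out. At the same level, 5 to 7 years with 20 % loss also gives about 310, so the source of the figure cannot be identified.

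**5. Deaths and power with the stated numbers.** Power = Φ(½ √D × ln 1.31 − 1.96). For 20 % loss, η = −ln 0.80 / 5 = 0.0446, and the Baxter death probability is 0.454 (5 years) or 0.503 (5 to 7 years). Under equal hazards it applies to both arms.

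| Base and loss | 5 years | 5 to 7 years |
|---|---|---|
| 620 analysed, no loss | 310 deaths, 66 % | 349 deaths, 71 % |
| 620 analysed, 15 % early loss | 289 deaths, 63 % | 321 deaths, 68 % |
| 750 enrolled, 20 % loss | 340 deaths, 70 % | 377 deaths, 75 % |

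**The case against.** The strongest reply is that the 15 % was never meant as total censoring. Survival, recruitment and observation time already determine how many patients are alive at the end, so an extra censoring term in that list most naturally means early loss, which is compatible with 50 % survival. This stands: the documents do not support saying that the input is impossible on every reading.

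A reader might also infer that losses are counted twice. That is not shown. The primary set is per-protocol, so 15 % could be early loss among analysed patients and 20 % the allowance for getting from enrolled to analysable patients. The text does not say this, but nothing rules it out. For the same reason, taking both percentages off 620 would be wrong, because it ignores the enrolment of 750 that the 20 % pays for.

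Nor can it be inferred that the authors counted on 620 × 0.85 = 527 deaths. That reading would have led them to about 254 per group, and they state 310.

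Two further replies carry weight. Follow-up is by calendar time, and a condensed article may leave an expected death count to the full protocol, so its absence is not the complaint. And most of the power shortfall is there before any loss (66 % at 5 years); the 15 % moves power by only about three points. What remains is that a printed input is wrong or mislabelled, and that the printed size does not follow from it on either reading.

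**Conclusion.** The point holds in limited form. As a total censored share, 15 % contradicts the article's own survival assumption. As early loss it is possible but undefined, and its relation to the 20 % is left open; double counting is not proven. On neither reading do the stated inputs yield 310 per group at one-sided 0.025 and 80 % power.

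Against about 431 deaths needed, the stated numbers lead to roughly 289 to 377, or 63 to 75 % power, depending on which loss figure and base apply and whether follow-up stops at 5 years or runs to 7. These figures rest on 1.31 being the bound, equal true hazards, and exponential survival and loss. The impossibility of 15 % total censoring at a fixed 5 years needs none of those assumptions; it follows directly from 50 % survival.

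**What to change.** In the Sample size section, replace the 15 % censoring phrase with two separate statements: the share expected to be alive and administratively censored (about 50 % on Baxter at 5 years), and the early-loss rate. Say what the 20 % covers, for instance exclusion from the per-protocol set or loss of vital status. Apply each rate once and to its proper base, 310 per group analysed or 750 enrolled. Then restate the expected number of deaths and the power they give, with the follow-up assumption (5 years, or 5 to 7) made explicit.

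The cost is a reworded paragraph and one recalculation. The correction itself requires no additional patients, but the stated power will become less favourable.

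### The stated 310 patients per group does not give 80 % power at one-sided 0.025: if 1.31 is the margin and the fluids are equal, power is about 63 to 71 %, or 59 % on the harshest allowance for loss

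*Protocol article*

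**What the plan says.** The Sample size section starts from the assumption that "the mean 5-year survival rate of patients using Baxter dialysis fluid is about 50" %, "with a hazard ratio of 1.31". It adds the timing ("If the recruitment lasts 2 years and the observation 5 years"), prints β = 0.8, gives "a one-sided *α* for the *t* test = 0.025", and allows for "15 % censored data in each group". From these it concludes that "310 patients per group will be needed", and raises the total to 750 for 20 % drop-out. No number of deaths is given.

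Three other places bear on the calculation. Under Study design the trial is declared non-inferiority. Under Statistics, non-inferiority of survival is judged by the 95 % confidence interval of a Cox hazard ratio, which matches a one-sided 0.025 test. Under Randomization, "Patients are centrally randomized 1:1". The Fig. 1 legend gives the treatment period: "Patients will use Baxter or HUAREN peritoneal dialysis fluid for 5 years".

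**The concern.** In a Cox or log-rank comparison, power depends on the number of deaths. The section prints all the main inputs and a result, so the result can be checked, and it does not follow. With half the control patients alive at 5 years, 620 patients cannot supply the deaths needed to exclude a hazard ratio of 1.31 with 80 % power.

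The reader is told that two equal fluids would be shown non-inferior four times in five. On 620 evaluable patients, the chance of missing non-inferiority is about 29 to 37 % (1 − 0.713 to 1 − 0.631), not 20 %. The Discussion presents the result as an aid to government policy and describes only two outcomes, non-inferior or inferior. An inconclusive interval is therefore a likelier outcome than the plan prepares its readers for.

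**Working it through.** **Inputs from the Sample size section:** control 5-year survival 50 %; hazard ratio 1.31; one-sided alpha 0.025; power 0.80 (β = 0.8 read as power); 2 years' recruitment and 5 years' observation; 15 % censoring; 310 per group, so 620; 750 enrolled. Allocation is 1:1 (Randomization).

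**Assumptions added here:** 1.31 is the margin; the true hazard ratio is 1; survival is exponential; loss to follow-up is exponential at the stated percentage over 5 years.

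**1. Trying to reproduce 310.** With the event rate taken from 50 % 5-year survival, no standard variant tried at one-sided 0.025 returns 310 per group. Two departures do return it:
- One-sided 0.05, event probabilities of 0.50 and 1 − 0.5^1.31 = 0.597 (mean 0.548), no censoring allowance: 4(1.645 + 0.842)² / (ln 1.31)² = 339.2 deaths; 339.2 / 0.548 / 2 ≈ 309 per group.
- One-sided 0.025 with a 70 % event fraction: 431 / 0.70 / 2 = 308 (Schoenfeld) or 436 / 0.70 / 2 = 311 (Freedman).

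The first departs from the stated alpha, the second from the stated survival.

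**2. Deaths needed.** Schoenfeld: 4(1.960 + 0.842)² / (0.2700)² = 430.6, so 431. Freedman: (2.31 / 0.31)² × (1.960 + 0.842)² = 435.8, so 436. As a share of 620, 431 is 69.5 %.

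**3. Deaths expected.** Death hazard λ = ln 2 / 5 = 0.1386 per year. Loss hazard γ = −ln(1 − loss) / 5, which is 0.0325 for 15 %. The probability of an observed death by time t is λ/(λ+γ) × [1 − exp(−(λ+γ)t)], taken at t = 5, or averaged over t from 5 to 7 for uniform 2-year entry with everyone followed at least 5 years.

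**4. Power.** Φ(ln 1.31 × √d / 2 − 1.960). For d = 310: 0.2700 × 17.61 / 2 − 1.960 = 0.417, so 66.2 %.

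| Patients | Follow-up | Loss over 5 years | Deaths d | Power |
|---|---|---|---|---|
| 620 | 5 years | none | 310 | 66 % |
| 620 | 5–7 years | none | 349 | 71 % |
| 620 | 5 years | 15 % | 289 | 63 % |
| 620 | 5–7 years | 15 % | 322 | 68 % |
| 620 | 5 years | deaths cut by 15 % | 264 | 59 % |
| 750 | 5 years | 20 % | 340 | 70 % |
| 750 | 5–7 years | 20 % | 377 | 75 % |
| 750 | 5 years | 15 % | 349 | 71 % |
| 750 | 5–7 years | 15 % | 389 | 76 % |
| 750 | 5–7 years | none | 422 | 79 % |

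**5. Hazard ratio that can be excluded with 80 % power.** exp(2 × 2.802 / √d). On 620 with 15 % loss: d = 289 gives 1.39 and d = 322 gives 1.37. On 750 with 15 to 20 % loss: d = 340 gives 1.355 and d = 389 gives 1.33.

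**6. The literal reading of 15 % censored.** If only 15 % of patients were censored, 85 % would die: 0.85 × 620 = 527 deaths and 87 % power. That contradicts 50 % alive at 5 years, and would require only 430.6 / 0.85 / 2 ≈ 253 to 254 per group, so it does not explain 310.

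**The case against.** The strongest objection is that the section does not call 1.31 a margin and states no true hazard ratio, so the power figures are conditional. That stands. The choice can matter: with a true hazard ratio of 0.95 in favour of HUAREN, 620 patients followed 5 years without loss would give about 304 deaths and Φ((ln 1.31 − ln 0.95) × √304 / 2 − 1.960) ≈ 80 %. But 0.95 is not a planning value in the document, and even then cutting deaths by 15 % brings power to about 73 %. Reading 1.31 as an effect to be detected does not rescue 310 either: 431 deaths are still needed, and event probabilities of 0.50 and 0.597 give 340 deaths in 620 patients over 5 years, or 70 % power.

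A second objection is that drop-outs contribute deaths and follow-up until they leave, so the 750 enrolled should count. This is fair, and it is why those rows are shown. They narrow the gap without closing it. Passing 80 % with 750 at a true hazard ratio of 1 would take, for example, a full 7 years for every patient with no loss (466 deaths, 83 %), against the stated censoring and drop-out.

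A reader might infer that the sponsor sized the trial at one-sided 0.05. The document does not show this, and the 70 % event fraction fits equally well. A reader might also infer that weak power makes a positive result unreliable. It does not: the 95 % interval still controls a false claim of non-inferiority. What rises is the risk of an inconclusive trial.

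**Conclusion.** The sample-size statement is wrong as written. With 1.31 as the margin and a true hazard ratio of 1, about 431 deaths are needed, and 620 evaluable patients supply about 310 to 349 before loss. Power is 66 to 71 % without loss and about 63 to 68 % with 15 % loss over 5 years; it is 59 % if the 5-year deaths are simply cut by 15 %. On all 750 enrolled it is about 70 to 76 % with 15 to 20 % loss, and 79 % with none over 5 to 7 years.

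The range should not be quoted as following from the printed inputs alone: it also needs the margin reading, a true hazard ratio of 1, and a choice of follow-up and loss pattern. These choices move the size of the shortfall. None that keeps 50 % 5-year survival, a true hazard ratio of 1 and the stated 310 per group removes it.

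**What to change.** Rewrite the Sample size section as a log-rank or Cox non-inferiority calculation in events:
- replace the t-test label, and replace β = 0.8 with power of 80 %;
- say explicitly that 1.31 is the non-inferiority margin and which true hazard ratio is assumed;
- give the requirement of about 431 deaths, and say how follow-up and censoring enter;
- state either the power that the planned size delivers (at a true hazard ratio of 1, about 63 to 68 % on 620 evaluable with 15 % loss, about 70 to 76 % on 750 enrolled with 15 to 20 % loss), or the hazard ratio it can exclude with 80 % power (about 1.37 to 1.39 on 620, about 1.33 to 1.36 on 750).

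The second form describes what the size can do; it is not a proposal to widen the margin during the trial.

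The cost is revised wording and a less favourable stated power, with no extra patients. If the sponsor wants to keep 80 %, vital-status follow-up of enrolled patients could continue until 431 deaths. That is optional, has its own cost in time, and is not needed to correct the statement.

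### Enrolling 750 does not cover the stated 20 % drop-out: 620 evaluable patients would need 775, and 750 allows for only about 17 %

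*Protocol article*

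**What the plan says.** The Sample size section gives the size in two steps. The first ends with the requirement before drop-out: "310 patients per group will be needed". The second adds the drop-out allowance: with a 20 % "drop-out rate, 750 patients should be enrolled in this study".

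Allocation is equal (Randomization section: "Patients are centrally randomized 1:1 to HUAREN or Baxter peritoneal dialysis fluid"), so the first step means 620 patients in total. A 15 % censoring figure is listed among the inputs to the 310 ("15 % censored data in each group, 310 patients per group will be needed"), so the 20 % is a further allowance made after it. The article gives no other enrolment figure and does not explain how 750 was derived.

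**The concern.** A drop-out rate is ordinarily a proportion of the patients enrolled. To keep a required number after losing a proportion d, the requirement is divided by (1 − d). Multiplying by (1 + d) always gives too few, because the loss then applies to the larger, inflated number. The step from 620 to 750 looks like this slip.

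At stake is whether the headline enrolment figure delivers the number of patients that the same paragraph calls necessary. The error runs in the unfavourable direction, since the target falls below the plan's own requirement. Rounding cannot explain it, because 775 does not round up to 750.

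**Working it through.** **Inputs, all from the article**

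- Required per group: 310 (Sample size). Allocation 1:1 (Randomization). Total: 2 × 310 = 620.
- Drop-out rate: 20 % (Sample size).
- Stated enrolment: 750 (Sample size).
- One-sided alpha 0.025. Power 80 %, reading the printed β = 0.8 as power (Sample size).

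**Step 1. Try to reproduce 750**

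- Division by (1 − d): 620 / 0.80 = 775. By arm: 310 / 0.80 = 387.5, rounded up to 388, or 776 in total. This does not give 750; the stated figure is 25 to 26 patients lower.
- Multiplication by (1 + d): 620 × 1.20 = 744. Rounded up to a convenient number, this gives 750. It is the only one of the two routes that comes close.

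**Step 2. What 750 delivers**

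- Remaining after 20 % drop-out, every drop-out removed: 750 × 0.80 = 600, or 300 per arm.
- Shortfall against the requirement: 620 − 600 = 20 patients, and 20 / 620 = 3.2 %.
- Drop-out that 750 can absorb while keeping 620: 1 − 620/750 = 130/750 = 17.3 %.

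**Step 3. Effect on power**

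Take the plan at its word that 620 patients give exactly 80 % power, and assume the same proportion of patients die whether 600 or 620 are analysed. In a log-rank or Cox comparison the expected test statistic grows with the square root of the number of deaths, and so here with the square root of the number of patients.

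- Expected statistic at 620: 1.960 + 0.842 = 2.802.
- Expected statistic at 600: 2.802 × √(600/620) = 2.802 × 0.984 = 2.756.
- Power at 600: Φ(2.756 − 1.960) = Φ(0.796) = 78.7 %.

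The loss is about 1.3 percentage points. The hazard ratio does not enter this step, so the result does not depend on how the 1.31 is interpreted.

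**Step 4. Does the size of the loss depend on the starting power?**

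Only slightly. As a sensitivity check, assume that 1.31 is the margin, that the true hazard ratio is 1, and that the proportion dying lies between 50 % and 85 %. The Schoenfeld formula then gives, for 620 against 600 patients, 66.2 % against 64.7 % at the lower end (1.5 points) and 87.3 % against 86.2 % at the upper end (1.1 points). The levels rest on those assumptions and are not part of this point. What matters is that the difference stays between 1.1 and 1.5 points.

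**The case against.** The best defence is that 20 % was meant as a mark-up on the requirement and not as a share of those enrolled. On that reading 620 + 124 = 744, and 750 is slightly generous. This probably explains how the number arose, but it does not rescue the sentence, which calls the 20 % a drop-out rate. Read that way, 750 is too small.

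A second defence is that a patient who drops out is not necessarily lost. The Statistics section keeps in the per-protocol set those who leave because the treatment did not work, and a Cox model can use follow-up up to the time of leaving. This stands, and it rules out a stronger reading. A reader might infer that the primary per-protocol analysis will hold 600 patients. The article does not support that: 600 is the count if every drop-out is removed, and the set could turn out larger for the reasons above, or smaller if poor compliance removes others.

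Two further inferences should also be resisted.

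- That the slip leaves the trial seriously underpowered. Any absolute power level depends on how the hazard ratio of 1.31 is read and on how long patients are followed, neither of which the article makes precise. Whether 310 per group is itself adequate is a separate question. The drop-out step accounts for little more than one point.
- That the 15 % censoring and the 20 % drop-out count the same patients twice. The article lists the 15 % as an input to the 310 and does not define either group further. A condensed article commonly leaves such definitions to the full protocol, so their absence is not an error here.

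The defence that the shortfall is too small to matter is right about the consequence. It does not make the stated figure correct.

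**Conclusion.** The enrolment sentence is wrong as written, and the point is minor. From the article's own inputs, 620 patients after 20 % drop-out require 775 enrolled (776 with rounding by arm), not 750. The arithmetic is certain, given that the drop-out rate is a proportion of those enrolled. That the figure came from multiplying by 1.2 is a plausible explanation that the article does not confirm.

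The power cost, 80 % to about 78.7 %, rests on three assumptions: 620 patients give exactly 80 %, the proportion of deaths is unchanged, and every drop-out is lost to the analysis. If drop-outs contribute follow-up, the cost is smaller. The slip does not affect the choice of outcome, the analysis method or the interpretation of the result.

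**What to change.** Restate the sentence in one of two ways:

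- 750 patients will be enrolled, which leaves 600 evaluable (300 per group) at 20 % drop-out, with the matching power. That is about 78.7 % if 310 per group gives 80 %; the sponsor should recompute it with the method used for the 310.
- 750 patients will be enrolled, which allows for a drop-out of about 17 % while keeping 310 per group.

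Either version makes the requirement, the rate and the total agree. The cost is one corrected sentence. Recruitment, which the Trial status section describes as under way, need not change.
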